### Data Analysis and Sample Size

The number of participants to be involved was defined to test the superiority of walking football compared with usual care, using intention-to-treat analysis. For a 1:1 ratio of the intervention and control groups, significance level of 5%, and statistical power of 80%, a total of 162 participants will be needed to detect a mean difference of at least 0.35% in the primary outcome (glycated hemoglobin), based on previous meta-analyses [33,34]. Assuming the complete follow-up of at least 80% of the participants, a total of 200 participants will be enrolled.

We will use a 2-way (group*time) analysis of variance with repeated measures to compare the mean differences between intervention and control groups.

For the cost-utility analysis, we will calculate the walking football implementation costs compared with the usual care. Costs include technical training for the professionals involved, patients’ medical assessments, material for capillary blood glucose and blood pressure evaluations, football equipment, sports facility rental, sports insurance, and payment to nurses and football coaches. The costs of the intervention and reported gains in quality of life (based on quality-adjusted life years) [27] will be used to calculate the incremental cost-utility ratio (ICUR). ICUR will be compared with the World Health Organization thresholds for health interventions based on per capita gross domestic product.

The amount of missing data is expected to be low considering the training of all the staff and the use of standardized procedures for data collection. No imputation is being planned.

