**Methods:**

The study will be run as a randomized controlled trial with a 6-month duration in Portugal. Eligible participants will be randomized using a 1:1 ratio for intervention or control groups and compared using an intention-to-treat analysis. The intervention will consist of a walking football exercise program. The control group will continue with usual care in primary health care units. The primary outcome will be the mean difference in glycated hemoglobin between intervention and control groups after 6 months. Secondary outcomes include the mean differences in fasting blood glucose, total cholesterol, low-density lipoprotein cholesterol, high-density lipoprotein cholesterol, triglycerides, systolic and diastolic blood pressure, body mass index, waist circumference, fat-free mass, and fat mass. Additionally, secondary outcomes include the incidence of exercise-related injuries and adverse events and the walking football exercise program’s cost-utility.

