### Outcomes

The primary outcome is the difference in the change in glycated hemoglobin level between intervention and control groups after 6 months. Secondary outcomes include changes between groups in fasting blood glucose, total cholesterol, low-density lipoprotein cholesterol, high-density lipoprotein cholesterol, triglycerides, systolic and diastolic blood pressure, body mass index, waist circumference, fat-free mass, and fat mass.

Secondary outcomes also include the incidence of exercise-related injuries and adverse events, as well as the cost-utility of the walking football exercise program.

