### Data Collection

Data collection will have 3 main time points: baseline (before starting the study), 6 months (after the study ends), and every walking football exercise session. The descriptions of the variables assessed at baseline and the 6-month evaluation are presented in Table 1.

**Table 1 table1:** Variables assessed at baseline and at the end of the study.

Variable		Method

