**Glycemic control**		
	Glycated hemoglobin	Venous blood analysis
	Fasting blood glucose	Venous blood analysis

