**Body composition**		
	Fat mass	Bioelectrical impedance analysis
	Fat-free mass	Bioelectrical impedance analysis
Habitual physical activity		Global Physical Activity Questionnaire score [26]
Dietary intake		3-day food record, 24-hour dietary recall analysis
Health-related quality of life		EQ-5D questionnaire [27]
Medication (number, type, and dosage)		Form

^a^LDL: low-density lipoprotein.

^b^HDL: high-density lipoprotein.

Before and after the study, habitual physical activity, dietary intake, health-related quality of life, and regular medication will be collected to be used as control variables. We will also collect sociodemographic characteristics at baseline.

At every exercise session, objective and subjective exercise intensity and enjoyment will be recorded for control purposes.

The descriptions of the variables to be assessed before, during, and after each exercise session are detailed in Table 2. Capillary blood glucose, blood pressure, and feet wounds will be assessed before the exercise session; objective exercise intensity will be recorded during the exercise session; subjective exercise intensity and enjoyment will be assessed at the end of the exercise session; and exercise-related injuries and adverse events will be evaluated during and after the exercise session if participants report symptoms or the nurse notices any issue.

**Table 2 table2:** Variables assessed in each exercise session.

Variable		Method
Pre-exercise capillary blood glucose		Glucometer
Pre-exercise blood pressure		Automatic digital sphygmomanometer
Pre-exercise feet wounds		Self-observation

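### The two-visit group-by-time ANOVA for HbA1c is a valid change-score test, but adjusting for the baseline HbA1c already collected would generally be more precise at no cost

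*Protocol article*

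**What the plan says.** The only analysis sentence for the clinical outcomes is in Data Analysis and Sample Size. It plans a two-way group-by-time "analysis of variance with repeated measures to compare the mean differences between intervention and control groups". It names no covariate.

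HbA1c is collected twice. Data Collection states that "The descriptions of the variables assessed at baseline and the 6-month evaluation are presented in Table 1", and that table lists "Glycated hemoglobin" by venous blood analysis. After Table 1 the article adds that "habitual physical activity, dietary intake, health-related quality of life, and regular medication will be collected to be used as control variables". Baseline HbA1c is not in that list, and the article does not say how the listed variables enter a model.

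The primary outcome is worded in two ways. The Abstract has: "The primary outcome will be the mean difference in glycated hemoglobin between intervention and control groups after 6 months". The Outcomes section has: "The primary outcome is the difference in the change in glycated hemoglobin level between intervention and control groups after 6 months".

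The sample size is 162 evaluable participants for a difference of 0.35 percentage points at 5% significance and 80% power, with 200 enrolled to allow for 80% follow-up. The article states no SD and no correlation between visits.

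**The concern.** With only two visits, a group-by-time repeated-measures ANOVA makes no more use of the baseline than subtraction does. Its interaction term compares mean change between arms, which amounts to assuming that a patient who starts one point higher will, untreated, finish one point higher. Where the true slope is below 1, two things follow.

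- **Precision.** Subtracting the whole baseline value adds noise that an estimated slope would leave out.
- **Chance imbalance.** If the arms differ by b at baseline and the true slope is β, the change-score estimate is off by (1 − β)b in that dataset through regression to the mean. ANCOVA removes this.

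The same sentence covers the 11 continuous secondary outcomes, so any loss applies to them too. The plan has little slack: the expected completers are 0.80 × 200 = 160, just under the 162 required.

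**Working it through.** **1. Reproduce the plan's figure.** Inputs from Data Analysis and Sample Size: 81 per arm, difference 0.35, 5% significance, 80% power. Two-sided testing is my assumption, because sidedness is not stated. No SD is given, so 162 cannot be reproduced independently, but the SD can be back-solved:

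SD = 0.35 / [(1.960 + 0.842) × √(2/81)] = 0.795 by the normal formula, or 0.790 by the t test.

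So 162 is consistent with an SD of about 0.79 to 0.80. The article does not say whether this is the SD of change or of a single visit. With 80 completers per arm and SD 0.790, power is 79.5%.

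**2. The planned test is a change-score test.** On simulated two-visit data with 81 per arm, the group-by-time F was 12.3989 and the squared two-sample t on change scores was 12.3989. This identity applies to patients with both visits.

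**3. Variance with equal visit SDs.** With common SD s and correlation r:

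- change score: 2s²(1 − r)
- ANCOVA: s²(1 − r²)
- ratio ANCOVA/change: (1 + r)/2

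Taking 0.790 as the SD of change, with 80 completers per arm (r is assumed):

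| r | Variance ratio | Change-score completers that 160 under ANCOVA are worth | Power, change score | Power, ANCOVA |
|---|---|---|---|---|
| 0.5 | 0.75 | 160/0.75 = 213 | 79.5% | 89.5% |
| 0.6 | 0.80 | 160/0.80 = 200 | 79.5% | 87.5% |
| 0.7 | 0.85 | 160/0.85 = 188 | 79.5% | 85.5% |
| 0.8 | 0.90 | 160/0.90 = 178 | 79.5% | 83.5% |

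**4. If the implied SD is a single-visit SD instead.** With 0.795 at each visit and 162 evaluable, power by change score and by ANCOVA is 65.8% and 83.6% at r = 0.3, 80.0% and 89.9% at r = 0.5, and 95.1% and 97.5% at r = 0.7.

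**5. Unequal visit SDs.** Entry is restricted to HbA1c of 6.0% to 10.0% and follow-up is not, so the baseline SD (s0) may be smaller than the 6-month SD (s1). The general ratio is

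s1²(1 − r²) / (s0² + s1² − 2r·s0·s1).

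For s0/s1 = 0.9 (assumed):

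- r = 0.6: 0.64/0.73 = 0.88
- r = 0.7: 0.51/0.55 = 0.93
- r = 0.8: 0.36/0.37 = 0.97

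For s0/s1 = 0.8 and r = 0.8, the ratio is 0.36/0.36 = 1. The true slope is then r·s1/s0 = 0.8/0.8 = 1, exactly what the change score assumes, and ANCOVA gains nothing.

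**6. Size of the imbalance error.** Assume SD 1.0 at both visits, r = 0.5 and 80 per arm. One standard error of the baseline difference is √(2/80) = 0.158. The resulting shift is (1 − 0.5) × 0.158 = 0.08, a little under a quarter of the 0.35 target.

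**The case against.** The strongest reply is that nothing here is wrong. Under 1:1 randomisation the change-score test keeps its type I error, is unbiased on average, and estimates exactly what the Outcomes section defines. That stands. It is why this is a recommendation on precision and not a challenge to validity.

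The second reply is that the benefit cannot be determined from the article, because neither SD nor r is given and the entry window makes equal SDs doubtful. That also stands. The gain is conditional and may be close to nil. But with slope and correlation unknown, estimating the slope is the safer choice: in large samples ANCOVA is never less efficient than the change score.

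Three stronger readings are tempting, and the article does not support them.

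- **That the trial is underpowered because of this choice.** If 0.79 is the SD of change, the planned test has essentially its design power. Low power appears only under assumptions from outside the article. For example, SD 1.0 and r = 0.6 give 69% by change score, and ANCOVA then reaches only 78.5%.
- **That the group main effect might be taken as the primary test.** It averages baseline with follow-up and so halves the treatment effect. But the analysis sentence names group-by-time and the Outcomes section defines a difference in change. Together they point to the interaction.
- **That the Abstract and the Outcomes section define conflicting outcomes.** Under randomisation the difference at 6 months and the difference in change have the same expectation. As unadjusted estimates they will differ in a given dataset, so the wording should be aligned, but the treatment effect is the same.

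**Conclusion.** The point holds as a free improvement. The article itself fixes an unadjusted two-visit ANOVA, so this is not a detail left to an unseen analysis plan, and adjustment for baseline HbA1c appears nowhere in it.

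With equal visit SDs and r of 0.5 to 0.8, the planned test gives up 10% to 25% of variance relative to ANCOVA, or 4 to 10 percentage points of power at 160 completers if the implied SD is that of change. With a baseline SD of 0.9 times the follow-up SD, the saving falls to between 12% (r = 0.6) and 3% (r = 0.8). At an SD ratio of 0.8 with r = 0.8 it vanishes. All of these rest on assumed correlations and SDs and on a two-sided test.

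A reader might infer that the primary analysis is invalid or biased, or that the sample size is wrong. Neither is shown.

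**What to change.** Replace the ANOVA sentence in Data Analysis and Sample Size with:

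> The primary analysis is a linear model of 6-month HbA1c on randomised group, adjusted for baseline HbA1c and PHCU (randomisation is within PHCU); the group coefficient with its 95% CI is the primary estimate. The same model with the corresponding baseline value is used for each continuous secondary outcome.

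Then state the primary outcome in the same words in the Abstract and the Outcomes section: the adjusted between-group difference in HbA1c at 6 months.

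The cost is wording only, with no new data, visits or participants. The article describes ethics submission as still in preparation and recruitment as not yet begun, so on that timetable the model can be fixed before any outcome data exist.

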**Exercise intensity**		
	Subjective	OMNI perceived exertion scale [28]
	Objective	Heart rate and time-motion tracking
Exercise sessions enjoyment		Physical Activity Enjoyment Scale [29]
Exercise-related injuries and adverse events		Observational/clinical/self-reported

All personnel involved in the study — nurses, nutritionists, medical doctors, football coaches, and sports scientists — will receive training before baseline assessments. This aims to standardize procedures.

Specifically, the principal investigator will provide training to the other research team members regarding the clinical assessments and forms.

The Portugal Football School of the Portuguese Football Federation will provide training to football coaches to ensure the walking football program is administered in a similar way in the different centers and according to a predefined manual.

A sports scientist will monitor, in real time, internal (heart rate [HR]) and external (eg, distance covered, number of actions) workload and apply the OMNI perceived exertion scale in all sessions.

The nurse must have training in emergency procedures, be responsible for measurements at exercise sessions, manage and record exercise-related injuries and adverse events, follow-up with participants, and refer to health care facilities if necessary.

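### The cost-utility ratio is called incremental but its numerator is programme cost only, which is right only if medication and other care costs are equal in the two arms; the protocol neither states nor checks this

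*Protocol article*

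**What the plan says.** All costing text is in the protocol article, Data Analysis and Sample Size. It announces a comparison: "we will calculate the walking football implementation costs compared with the usual care". The list opens with "Costs include technical training for the professionals involved", continues with medical assessments, glucose and blood pressure test material and football equipment, and ends with "sports facility rental, sports insurance, and payment to nurses and football coaches". The inputs to the ratio are then given as "The costs of the intervention and reported gains in quality of life (based on quality-adjusted life years"), and the decision rule follows: "ICUR will be compared with the World Health Organization thresholds for health interventions based on per capita gross domestic product".

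Three other places bear on this:

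- Intervention and Control Groups asks both arms to keep their diabetes consultations and drug regimen.
- Table 1 lists "Medication (number, type, and dosage") and the EQ-5D, both taken at baseline and 6 months. The text below the table describes both as control variables.
- Data Collection states "A sports scientist will monitor, in real time, internal (heart rate [HR]) and external (eg, distance covered, number of actions) workload", at all sessions. The pay that is costed is for nurses and coaches.

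**The concern.** An incremental ratio divides a between-arm difference in cost by a between-arm difference in QALYs. Here the numerator is the cost of one arm's programme. Anything else that differs between the arms in cost, such as a change in medication or in use of care, drops out. Medication is the clearest case: the trial sets out to alter glycaemic control, and the data needed to price medication are already on a form, but the costing paragraph gives them no role.

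The denominator is loosely fixed as well. Reported gains could mean a within-arm change, a raw difference between arms, or an adjusted one, and these can differ when the expected gain is small.

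Cost-utility is the third specific objective and a named secondary outcome. The Discussion links a good ratio to the programme's case as a sustainable strategy. The ratio is to be read against a threshold, so a shift in either direction could change the reading.

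**Working it through.** The document gives no cost, QALY or ratio figure, so there is nothing to reproduce. The check compares the stated construction with the definition and then shows how sensitive the ratio is.

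**1. Definition against text.** Let P be programme cost per man in the intervention arm and B the mean background cost (medication, consultations, other care) in each arm.

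- Incremental cost = (P + B_int) − B_ctl = P + d, where d = B_int − B_ctl.
- The plan's numerator = P.
- The two agree only if d = 0.

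The instruction to continue usual care makes d = 0 plausible as a starting point. It is an instruction to participants, not a stated costing assumption, and no check of d is planned.

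**2. Size of the denominator.** With utility changing linearly over half a year, a gain Δ at 6 months gives 0.5 × 0.5 × Δ = 0.25Δ QALY. Δ is not in the document; 0.03 to 0.05 is assumed.

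- Δ = 0.03: 0.25 × 0.03 = 0.0075 QALY
- Δ = 0.05: 0.25 × 0.05 = 0.0125 QALY

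**3. Leverage of an unmeasured cost difference.** The ratio shifts by d divided by the QALY gain. For d = EUR 10 per man:

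- 10 / 0.0125 = 800 per QALY
- 10 / 0.0075 = 1,333 per QALY

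Illustration with all values assumed: P = EUR 500, gain 0.0125 QALY.

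| d (EUR per man) | (500 + d) / 0.0125 |
|---|---|
| −200 | 24,000 |
| 0 (as planned) | 40,000 |
| +200 | 56,000 |

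**4. Baseline imbalance in EQ-5D.** With 80 followed per arm (200 × 0.80 / 2) and an assumed SD of 0.20, the standard error of the baseline difference is 0.20 × √(2/80) = 0.0316. If the correlation between baseline and 6-month EQ-5D is r, a one-SE imbalance carries 0.25 × 0.0316 × (1 + r) into an unadjusted QALY difference.

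- r = 0: 0.0079
- r = 1: 0.0158

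This exceeds 0.0125 only if 1 + r > 0.0125 / 0.0079 = 1.58, that is, r above about 0.58. It exceeds 0.0075 for any r of zero or more. Chance imbalance can therefore be of the same order as the gain, but it is not larger under every assumption.

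**5. Session monitoring.** Five groups × 72 sessions × 1 h = 360 h, or 3.6 h for each of 100 intervention participants, assuming one sports scientist per session. At an assumed EUR 10 to 30 per hour this is EUR 36 to 108 per man. At EUR 20 it is EUR 72, and the illustrative 40,000 becomes (500 + 72) / 0.0125 = 45,760.

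**The case against.** The strongest reply is that the programme is an add-on. Both arms are asked to keep consultations and medication as they are, so shared costs cancel and programme cost is the incremental cost. This stands as far as it goes. A reader might infer that the planned ratio is simply not incremental; the documents do not support that, because the comparison with usual care is announced and the ratio is incremental when d = 0. What remains is that d = 0 is neither declared nor examined.

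The cost list opens with a verb that need not be exhaustive, and a journal article may leave costing perspective and unit costs to a fuller document. The control-variable label does not rule out costing medication either, since EQ-5D carries the same label and still feeds the QALYs. These points soften the reading. The text that is present still names the numerator, and it names programme cost.

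A reader might also infer that leaving out the sports scientist is an error, or part of why the ratio is not incremental. Neither follows. Omitting a programme item understates programme cost without changing the type of ratio. The omission itself is defensible: Intervention and Control Groups names only a coach and a nurse as supervisors, and Data Collection says intensity is recorded for control purposes, which fits a research cost. The protocol does not say so.

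Nor can it be said that injury care is absent. The nurse, whose pay is costed, manages injuries and adverse events. Sports insurance is costed, and Ethics and Dissemination describes insurance for exercise risks. Adding injury care without regard to these could count it twice.

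**Conclusion.** The point holds as a gap in definition. The numerator is programme cost, and it matches the incremental label only on an unstated and unchecked assumption of equal medication and other care costs. The QALY term is not fixed as a baseline-adjusted between-arm difference.

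The size and direction of any error cannot be calculated from the document. The shifts of 800 to 1,333 per QALY for each EUR 10 rest on assumed EQ-5D gains and a linear path. The baseline-imbalance figures rest on an assumed SD and depend on r. None of them shows that the ratio would cross a threshold, whose value the document does not give. It would also be wrong to infer that the protocol concludes that cost-utility is good; it states this only as an expectation.

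The primary outcome and the clinical secondary outcomes are untouched. The change is worth making now because, per Results, recruitment has not begun.

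**What to change.** In Data Analysis and Sample Size:

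1. Define ICUR = (mean cost intervention − mean cost control) / (mean QALY intervention − mean QALY control).
2. Define cost as programme cost plus medication, priced from the Table 1 form at baseline and 6 months and interpolated between them.
3. Estimate the QALY difference by regression on baseline EQ-5D and PHCU. Randomisation is within PHCU, and baseline EQ-5D is already collected.
4. State that other care costs are assumed equal between arms, or include PHCU contacts where records allow. In the second case, do not count again any injury care already covered by insurance or nurse pay.
5. Declare the sports scientist and heart-rate telemetry a research cost, and add a sensitivity analysis that includes them.

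Items 1 and 3 cost wording only. Item 2 needs pricing and an interpolation assumption, because medication is recorded at two time points. PHCU contacts under item 4 would be new data extraction, so stating the assumption is the cheaper route. Item 5 needs an hourly rate and an equipment cost. The resulting ratio may be less favourable than the one now planned.

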## Discussion

### Overview

The main goal of this study is to test the effectiveness of a walking football program for glycemic control and cardiovascular risk factors in middle-aged and older male patients with T2D.

To the best of our knowledge, this is the first study testing the effects of a walking football exercise program for these outcomes in this specific population. Also, the investigation proposed relies on robust methodology, with a large study sample.

We expect that the walking football program will be effective in improving diabetes control and cardiovascular risk factors. We also expect a low rate of exercise-related injuries and adverse events and a good cost-utility ratio, as observed in other studies testing the effect of physical activity on diabetes control [35-38].

Developing an effective program with a good cost-utility ratio may contribute to making walking football a sustainable intervention strategy for T2D control. In addition, it can be used by football clubs to offer these programs as a service to their communities, ultimately contributing to the sustainability of the intervention and scaling up the offer to population coverage.

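### Cost-utility is to be judged by setting an ICUR against GDP-based thresholds, but that ratio is unstable when the 6-month QALY difference may be near zero or negative; incremental net benefit with an interval would be sounder

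*Protocol article*

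**What the plan says.** The Outcomes section makes cost-utility a secondary outcome: "Secondary outcomes also include the incidence of exercise-related injuries and adverse events, as well as the cost-utility of the walking football exercise program". It is also the third specific objective.

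The method is in Data Analysis and Sample Size. On the cost side, "we will calculate the walking football implementation costs compared with the usual care". The items listed are staff training, medical assessments, monitoring materials, football equipment, facility rental, insurance, and nurse and coach pay. No savings elsewhere in care are listed. On the effect side, the sentence that introduces the ICUR (incremental cost-utility ratio) names its two components: "The costs of the intervention and reported gains in quality of life (based on quality-adjusted life years) [27] will be used to calculate". Then comes the threshold step: "ICUR will be compared with the World Health Organization thresholds for health interventions based on per capita gross domestic product".

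Table 1 gives EQ-5D as the quality-of-life instrument. The Data Collection section places the trial-level assessments at "baseline (before starting the study), 6 months (after the study ends"). The Overview of the Discussion states the expectation: "We also expect a low rate of exercise-related injuries and adverse events and a good cost-utility ratio".

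The article gives no cost figure, no GDP figure or multiple, no EQ-5D standard deviation, and no numerical pass mark.

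**The concern.** The article fixes two things: the statistic is a ratio, and the comparator is a threshold. A ratio serves well when the QALY difference is clearly positive. This trial may not be in that position. The numerator is positive almost by construction. The denominator is a difference in QALYs accrued over only half a year, and the plan describes it only as a gain.

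Two problems follow:

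- As the QALY difference passes through zero, the ICUR jumps from very large positive to very large negative. A trivial change in EQ-5D can therefore move the result from one extreme to the other.
- A negative ICUR at positive cost means that the programme costs more and loses QALYs. Numerically it lies below every positive threshold, so its position against the threshold carries no useful meaning.

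A confidence interval around the ICUR does not cure this when the denominator may cross zero. At stake is the statement on cost-utility, which the Discussion links to sustaining and scaling up the programme.

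**Working it through.** The plan gives no error rate or expected value for this comparison, so there is no figure of its own to reproduce. The check asks how a comparison of the point estimate with a threshold behaves when the programme has no QALY effect.

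**Inputs from the article.** 200 men randomised 1:1 gives 100 per arm. Complete follow-up of at least 80% gives 80 per arm. EQ-5D is measured at 0 and 6 months.

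**Assumed inputs, not in the document.** Utility SD s = 0.10 to 0.20; correlation between baseline and 6 months r = 0.5 to 0.7; incremental cost ΔC = EUR 200 to 1,000 per man; threshold λ = EUR 20,000 to 60,000 per QALY.

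**Standard error of the QALY difference.** With two utility measurements over half a year, QALY = 0.5 × (u0 + u1)/2 = 0.25 × (u0 + u1).

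- Unadjusted SD = 0.25 × s × √(2 + 2r)
- Baseline-adjusted SD = 0.25 × s × √(1 − r²)
- SE = SD × √(2/n), with n per arm

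**Probabilities under no QALY effect.** Take ΔQ ~ N(0, SE), ΔC > 0 and k = ΔC/(λ × SE).

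- Dominated results read as unfavourable: favourable if ΔQ > ΔC/λ, so P = 1 − Φ(k).
- Bare inequality ICUR < λ: every ΔQ < 0 also counts, so P = 0.5 + [1 − Φ(k)].
- Lower 95% limit of net benefit above zero, ΔC treated as fixed: P = 1 − Φ(k + 1.96).

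**Central case** (s = 0.15, r = 0.6, n = 80, ΔC = 500, λ = 60,000, baseline-adjusted).

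- SD = 0.25 × 0.15 × √(1 − 0.36) = 0.030
- SE = 0.030 × √(2/80) = 0.00474
- ΔC/λ = 500/60,000 = 0.00833, so k = 0.00833/0.00474 = 1.76

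| Reading | P(favourable), no QALY effect |
|---|---|
| Point estimate, dominated results excluded | 0.04 |
| Bare inequality ICUR < λ | 0.54 |
| Lower 95% limit of net benefit > 0 | 0.0001 |

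A simulation of 200,000 draws gave 0.040, 0.538 and 0.00008.

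**Range with dominated results excluded.**

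- Unadjusted: near 0 up to 0.41. The top is at s = 0.20, r = 0.7, n = 80, EUR 200, EUR 60,000: SE = 0.25 × 0.20 × √3.4 × √(2/80) = 0.01458; k = 0.00333/0.01458 = 0.23; P = 0.41.
- Baseline-adjusted: near 0 up to 0.31. The top is at s = 0.20, r = 0.5 with the same n, cost and threshold: SE = 0.25 × 0.20 × √0.75 × √(2/80) = 0.00685; k = 0.49; P = 0.31.

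**Effect of adjustment alone.** In the central case without baseline adjustment, SE = 0.25 × 0.15 × √3.2 × √(2/80) = 0.01061; k = 0.79; P = 0.22, against 0.04 with adjustment.

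**Bare inequality across the same grid.** 0.50 to 0.91. The floor of 0.50 does not depend on the assumed values. It comes wholly from counting the negative-QALY half as favourable.

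**The case against.** The strongest reply is that the article states no decision rule. It says that the ICUR will be compared with thresholds, and gives no inequality and no instruction on negative ratios. A reader might infer that a costlier, QALY-losing programme would be called cost-effective, and hence that a programme with no effect would pass at least half the time. The article does not support that. It speaks of gains, so a QALY loss is a case that it does not address, and a health economist would normally report such a result as dominated. This part of the reply stands.

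A second reply is that a condensed article commonly leaves intervals, bootstrapping and dominance conventions to a fuller document, so their absence is no fault. That also stands, and it means that the article does not show the conclusion resting on a point estimate alone. It does not answer the remaining point, which concerns what is stated: the quantity chosen for the comparison is a ratio.

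A third reply is that the 41% end is an extreme corner. It needs EUR 200 per man, which over 72 sessions is 200/72 ≈ EUR 2.80 per session for coach, nurse, facility and the rest. That is fair. Higher costs push the figure towards zero, and the low end of the range is then the more plausible.

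Finally, cost-utility is secondary, no error rate is claimed for it, and the Discussion voices an expectation, not a finding. This limits the importance of the point but does not remove it.

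**Conclusion.** The point holds in a limited form. The stated method sets an ICUR against GDP-based thresholds where incremental cost is almost surely positive and the 6-month QALY difference may be near zero or negative. The ratio is then unstable, and its negative values cannot be ranked against a threshold.

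The figure to carry forward is the one with dominated results read correctly. The at-least-one-half figure applies only to a bare inequality, which the article does not state, and should not be presented as the plan's rule. Both calculations assume no QALY effect, a normally distributed QALY difference and a fixed positive cost. The size cannot be settled from the article.

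This is a choice of analysis for a secondary outcome that is worth changing while recruitment has not begun. It does not touch the glycated hemoglobin comparison.

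**What to change.** In Data Analysis and Sample Size, replace the ICUR-against-threshold comparison as the basis for the cost-utility statement with incremental net monetary benefit:

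- At each GDP-based threshold already planned, compute threshold × incremental QALY − incremental cost.
- Estimate it from the participants' EQ-5D and cost data, adjusted for baseline EQ-5D.
- Report a bootstrap 95% interval and the probability that net benefit exceeds zero, and base any favourable statement on these.
- Report the ICUR descriptively, and only when incremental QALYs are positive. When QALYs are lost at higher cost, report the programme as dominated.

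Net benefit is defined and continuous for any sign of the QALY difference, so both problems with the ratio disappear. The cost is a few sentences of plan wording and a short bootstrap on EQ-5D and cost information already planned; no new data or patients are needed. The downside is that the cost-utility statement may be less definite than a single ratio suggests.
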